## Outcome measures

Outcome measures will be collected from participants in both intervention and control groups at baseline (following consent, prior to randomisation and group allocation) and at 12-14 weeks post completion of the 8-week programme or at an equivalent time for the control group. We acknowledge that a longer follow-up period would be desirable but funding does not permit follow-up beyond this.

Each participating practice will be assigned a Research Assistant responsible for outcome assessment on all participating patients within that practice. To enhance the quality of measurements, all Research Assistants will undergo a one-day Research Assistant Preparation Programme consisting of:

i) Training on the procedures and protocols surrounding the delivery, assessment and recording of all outcome measurements;

ii) Discussion on adverse events and their management;

iii) Simulated completion of all data collection instruments and forms;

iv) Basic Life Support training (for those requiring certification);

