## Sample Size Estimation

We used methods for standard sample size estimates for trials that randomised at the level of the individual [30] adjusting for clustering by inflating sample size estimates by the design effect given by $1+(\bar{n}-1)\rho$, where $\bar{n}$ is the average cluster size, and ρ is the estimated intraclass correlation coefficient (ICC) [31]. Sample size estimates are based on the primary outcome of health status as measured by the CRQ [23], expressed as the mean rate difference between intervention and control groups.

Previous work suggests 0.5 as the minimal clinically important mean difference for all four dimensions of the CRQ [32] and estimates of standard deviations of 1.145 (given as arithmetic mean of 0.88, 1.06, 1.24 and 1.40 for the Dyspnoea, Fatigue, Emotion and Mastery dimensions of the CRQ respectively) [33]. Using these values and the upper value of 0.05 from a range of ICC values identified within studies involving the older person in primary care, [34] calculations indicate that 32 practices with a minimum of 10 participants per practice are required, in total, to be randomised to control and intervention arms for power of at least 80% with alpha levels of 0.05. This allows for participant loss to follow-up of 20% plus a loss of 4 practices. ICC values lower than 0.05 would increase the power of the study.

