## Quantitative Analysis

The analysis will be based on the GP Practice with the patient as the unit of analysis whilst accounting for the intracluster correlation coefficient. Analyses will be by intention to treat. Quantitative data will be analysed, in aggregate, using The Statistical Package for the Social Sciences (SPSS, v17) and R ([37], 2.11). Data will be entered into SPSS, coded, cleaned and locked before any analyses are made. Only members of the research team who needed access to the database to fulfil their roles within the study were granted access to the database. Funders did not have access to the database at any time. Demographic characteristics of the practices and the participants within the practices will be described using percentages, measure of central tendency (means or medians) and measures of variation (standard deviations or ranges). Comparability of randomised groups by socioeconomic and other categorical baseline variables will be by the chi-square (*X*^2^) test.

Whilst every effort will be made to exclude all confounders at the design phase of the study, this is not always possible. The analysis of data will therefore include the search for and control of nuisance variables for which adjustments had not been made. In particular, a mixed effects model will be used to model the longitudinal change in the mean scores for each of the four dimensions of the CRQ primary response while adjusting for explanatory variables and baseline CRQ as needed and incorporating random effects to model the homogeneity within cluster and the correlation within patient across time. The Akaike information criterion (AIC), for linear mixed-effects models in the analysis of clustered data, will be used to decide between candidate models [38]. The significance level will be set at α = 0.05 for all analyses.

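### With only two CRQ time points, the planned mixed model lets baseline CRQ be both a response and a covariate, and the adjustment then does nothing for the treatment estimate

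*Protocol article*

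**What the plan says.** The Outcome measures section of the protocol article fixes two measurement occasions: "at baseline (following consent, prior to randomisation and group allocation) and at 12-14 weeks post completion of the 8-week programme", or an equivalent time for controls.

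The Quantitative Analysis section states that "a mixed effects model will be used to model the longitudinal change in the mean scores for each of the four dimensions" of the CRQ. The same sentence allows adjustment for explanatory variables and "baseline CRQ as needed and incorporating random effects to model the homogeneity within cluster and the correlation within patient across time". It goes on to say that AIC "will be used to decide between candidate models".

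The Sample Size Estimation section takes "0.5 as the minimal clinically important mean difference for all four dimensions of the CRQ", "estimates of standard deviations of 1.145" and "the upper value of 0.05 from a range of ICC values", for "power of at least 80% with alpha levels of 0.05". It takes no credit for baseline adjustment and gives no correlation between baseline and follow-up CRQ.

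**The concern.** With a single post-baseline value, a within-patient correlation over time exists only if the baseline value is one of the modelled responses. The sentence that implies this also offers baseline CRQ as a covariate. If both are done, the same number sits on both sides of the equation for half the data rows. An analyst could follow the text faithfully, report a baseline-adjusted result, and have an estimate that the baseline covariate had not changed, with a standard error that the covariate had made too small.

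Making the covariate optional is no safeguard. The stated selection rule is AIC, which rewards fit, and a covariate that reproduces half the responses fits very well.

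**Working it through.** **Inputs.** From the Sample Size Estimation section: difference 0.5, SD σ = 1.145 (σ² = 1.311), ICC 0.05, 32 practices of at least 10, 20% participant loss plus 4 practices. From Randomisation: 1:1 allocation. Assumed, because the article does not give it: baseline-to-follow-up correlation ρ of 0.3, 0.5 or 0.7. Also assumed: a practice effect that is the same at both occasions.

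**The plan's own figure.** Per arm without clustering: 2 × [1.145 × (1.960 + 0.842)/0.5]² = 82.3. With 8 of 10 patients retained, the design effect is 1 + 7 × 0.05 = 1.35. Then 82.3 × 1.35/8 = 13.9, so 14 practices per arm, 28 in total, plus 4 lost = 32. The figure reproduces (power 0.803, two-sided 0.05). The checks below use 14 practices × 8 patients = 112 per arm.

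**Step 1: the arm-by-time term.** A covariate that is constant within a patient drops out of the follow-up-minus-baseline contrast. With complete data, the arm-by-time coefficient is therefore the raw difference in mean change, with or without the covariate. In 60 simulated data sets at each of ρ = 0.3 and 0.5 (true effect 0.5), the two agreed to 4e-12, with means 0.491 and 0.473.

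**Step 2: cost in precision.**

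- Change score: variance = 4σ²(1 − ρ)/112.
- Analysis of covariance with a practice random intercept, using the within-practice slope b = (ρ − 0.05)/0.95: variance = 2σ²[(1 − b)² × 0.05/14 + 0.95(1 − b²)/112].

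| ρ | b | Change score | ANCOVA | Ratio |
|---|---|---|---|---|
| 0.3 | 0.263 | 0.0328 | 0.0258 | 1.27 |
| 0.5 | 0.474 | 0.0234 | 0.0198 | 1.18 |
| 0.7 | 0.684 | 0.0140 | 0.0128 | 1.10 |

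Simulation gave 1.28, 1.18 and 1.09. With no practice effect at all, the ratio is 2/(1 + ρ) = 1.54, 1.33 and 1.18, so the stable practice effect is the milder assumption.

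**Step 3: the standard error.** With baseline in both roles, its pooled slope is (1 + ρ)/2. The residual covariance between a patient's two rows is −σ²(1 − ρ)²/4. A patient random intercept cannot represent a negative covariance, so its variance is estimated at or near zero. The pooled residual variance is then σ²(1 − ρ)(3 + ρ)/4. The model variance of the within-patient contrast is twice this, against a true value of 2σ²(1 − ρ). The ratio of model to true variance is (3 + ρ)/4.

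| ρ | Variance ratio | SE ratio | SE too small by | Type I error |
|---|---|---|---|---|
| 0.3 | 0.825 | 0.908 | 9% | 7.5% |
| 0.5 | 0.875 | 0.935 | 6% | 6.7% |
| 0.7 | 0.925 | 0.962 | 4% | 5.9% |

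Type I error is 2[1 − Φ(1.96 × SE ratio)]. In the fitted mixed models, adding the covariate cut the mean SE from 0.180 to 0.163 (ρ = 0.3) and from 0.152 to 0.142 (ρ = 0.5), with the estimate unchanged. A separate set of 4,000 null trials per correlation, with the patient effect at zero and no practice effect fitted, gave 7.2%, 7.2% and 6.3%.

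**Step 4: what AIC does.** Maximum-likelihood AIC preferred the model with the baseline covariate in all 120 data sets, by about 214 points (ρ = 0.3) and 298 points (ρ = 0.5) on average.

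**Step 5: baseline in one role only.** Follow-up CRQ as sole response with the baseline covariate gave mean estimates of 0.514 and 0.465. Both occasions as responses with a common baseline mean gave 0.509 and 0.466. Neither form shrinks the effect.

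**The case against.** The double role is permitted by the text, not stated. Baseline adjustment is conditional, the candidate models are not listed, and a journal article may leave them to an analysis plan. Some readings escape: baseline as a response with no baseline covariate is sound, and adding a baseline-by-time term recovers the covariance-adjusted estimate (0.514 and 0.465). If the response is one change score per patient, adjustment works, although the patient random effect then cannot be separated from residual error. This stands, and it makes the harm conditional.

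It is also true that planned power is hardly threatened. The sample size assumes an unadjusted follow-up comparison. Relative to that, the change-score variance is 2(1 − ρ)/1.35 = 1.04, 0.74 and 0.44 at ρ = 0.3, 0.5 and 0.7. The loss is against a better analysis of the same data.

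A reader might infer that the estimated effect is halved. A pooled arm coefficient with no arm-by-time term, averaging over the pre-randomisation null and the follow-up effect, does give half: 0.257 against 0.514 and 0.232 against 0.465. But that is not a model of change, and the article does not propose it. Nor does it propose an unadjusted follow-up-only analysis, so the larger precision losses of that analysis are not chargeable to this plan.

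The objection does not remove the point. What is criticised is a stated rule, optional baseline adjustment settled by AIC inside a model with a patient-over-time effect, and that rule leans towards the defective choice.

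**Conclusion.** The point holds as a conditional weakness in the stated primary model. If baseline CRQ is used in both roles, the arm-by-time estimate remains unbiased but gains nothing from the adjustment. Its variance is about 1.1 to 1.3 times that of analysis of covariance, its model standard error is about 4 to 9% too small, and type I error is about 6 to 7.5% against the stated 5%.

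The identity with the change-score difference does not depend on the correlation; the sizes do. They rest on an assumed ρ of 0.3 to 0.7, a practice effect stable over time, and complete data on 28 practices of 8. The AIC preference was checked at ρ = 0.3 and 0.5 only, and the trial's actual candidate set is unknown. The documents support neither a biased arm-by-time estimate nor a halved effect. This is a free improvement.

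**What to change.** Pre-specify one primary model for each CRQ dimension, in one of two forms:

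- Follow-up CRQ is the only response; baseline CRQ is always a covariate; practice has a random intercept; there is no patient random effect; the arm coefficient is the treatment effect.
- Baseline and follow-up CRQ are both responses; the arms are constrained to a common mean at baseline; there is no baseline covariate; practice and patient have random effects; arm-by-time is the treatment effect.

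In either case, delete *as needed* in respect of baseline CRQ and take baseline adjustment out of the AIC selection. If the first form is chosen, drop the reference to longitudinal change as well. The cost is a sentence or two of analysis text. No further data are needed, and the 32 practices stay as planned.

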PR programmes have been predominantly hospital or home based, although provision in the primary health care setting has been recommended [14,15]. To date, only one trial evaluating the effects of pulmonary rehabilitation on exercise tolerance and quality of life in people with COPD in the primary care setting has been identified [16]. This study included participants with asthma (n = 23) and COPD (n = 43). The pulmonary rehabilitation programme was delivered by a physiotherapist and included exercise classes, breathing techniques and relaxation activities. Of the 99 participants randomised, 23 subsequently withdrew and their outcomes were unavailable for analysis. Of those remaining, outcome data on quality of life (QoL) as measured by the dyspnoea, fatigue, emotion and mastery components of the Chronic Respiratory Disease Questionnaire (CRDQ) are available for only 23 participants. This study concluded that pulmonary rehabilitation for patients with COPD or asthma delivered in local practices improves exercise tolerance and quality of life.

The effectiveness of structured education pulmonary rehabilitation programmes delivered at the level of the general practice on the health status of people with COPD remains uncertain and there is a need for a robust and fair assessment of this. The PRINCE study will provide this assessment and will also give people with COPD an opportunity to voice their experiences of living with COPD and their approach to self-management.

Our proposed intervention, a structured education pulmonary rehabilitation programme, is delivered at the level of the general practice and is provided to a group of people with COPD rather than to individual patient participants. Therefore, the proposed trial is clustered at the GP practice level.

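### On its plainest reading, the two-visit CRQ model leaves practice-level clustering of change out of the primary test; the plan should fix a model that keeps it in

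*Protocol article*

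**What the plan says.** All references are to the protocol article.

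- **Stated intent.** Quantitative Analysis opens: "The analysis will be based on the GP Practice with the patient as the unit of analysis whilst accounting for the intracluster correlation coefficient".
- **Model.** The same section describes a mixed model of longitudinal change in each of the four CRQ dimensions, "incorporating random effects to model the homogeneity within cluster and the correlation within patient across time". Baseline CRQ and other covariates are adjusted for only where judged necessary. AIC decides between candidate models, which are not listed. On error rate: "The significance level will be set at α = 0.05 for all analyses".
- **Visits.** Outcome measures gives two assessments: baseline, and 12-14 weeks after the end of the eight-week programme.
- **Sizing.** Sample Size Estimation describes "adjusting for clustering by inflating sample size estimates by the design effect", with ICC 0.05, for "power of at least 80% with alpha levels of 0.05".
- **Reason for clustering.** Background says the programme "is provided to a group of people with COPD rather than to individual patient participants. Therefore, the proposed trial is clustered at the GP practice".

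**The concern.** With two assessments, a correlation within patient across time can be estimated only if both visits are responses. The effect on change is then the arm-by-time term. A practice effect and a patient effect that take the same value at both visits subtract out of every patient's change score. What remains is a patient-level comparison of change with no allowance for practice.

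Clustering of change is what this design should expect. A nurse and a physiotherapist deliver the programme to a group at each practice, the Control Group section concedes that usual care may vary, and practices enter in four groups over time. If practices differ in how much their patients change, the confidence interval for the primary effect would be too narrow and the 0.05 level would not hold on any of the four dimensions. The power in Sample Size Estimation would also belong to a different analysis from the one run.

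**Working it through.** **1. The plan's own figure.** Inputs from Sample Size Estimation: difference 0.5, SD 1.145, ICC 0.05, 80% power, alpha 0.05 (taken as two-sided), 10 patients per practice, 20% patient loss, 4 practices lost.

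- Per arm before clustering: 2 × (1.96 + 0.8416)² × 1.145² / 0.5² = 82.3.
- Patients left per practice: 10 × 0.8 = 8. Design effect: 1 + 7 × 0.05 = 1.35.
- 82.3 × 1.35 = 111.1 per arm; 111.1 / 8 rounds up to 14 practices per arm, 28 in total; 28 + 4 = 32, as printed. Power at 14 × 8 per arm is 80.3%.

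So the printed power is for a comparison that allows for practice.

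**2. Does the practice intercept reach the change contrast?** This is an exact generalised least squares calculation for 14 practices × 8 patients per arm and two visits. Total variance is scaled to 1, with assumed patient variance 0.76 and residual variance 0.19.

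| Practice variance | Practice-by-time variance | SE of arm-by-time |
|---|---|---|
| 0.05 | 0 | 0.0824 |
| 0 | 0 | 0.0824 |
| 0.025 | 0.025 | 0.118 |

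The closed form for the first two rows is √(4 × 0.19 / 112) = 0.0824, which is the SE of an unclustered comparison of change scores. Only a practice-by-time component alters it. The ratio of the last row to the others is not the error inflation, because a fitted intercept-only model would absorb part of that component into its residual. Step 3 allows for this.

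**3. Error rate of the intercept-only test.** Let ρ = 0.05 be the score ICC and m = 8. Let CAC be the correlation between a practice's effects at the two visits, and IAC the corresponding patient-level correlation. The documents give neither, so both are assumptions.

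- ICC of change = ρ(1−CAC) / [ρ(1−CAC) + (1−ρ)(1−IAC)]
- Design effect = 1 + (m−1) × ICC of change
- Error = 2[1 − Φ(1.96/√design effect)]

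| CAC | IAC | ICC of change | Design effect | Error |
|---|---|---|---|---|
| 1.0 | any | 0 | 1.00 | 5.0% |
| 0.8 | 0.5 | 0.01/0.485 = 0.021 | 1.14 | 6.7% |
| 0.8 | 0.8 | 0.01/0.20 = 0.050 | 1.35 | 9.2% |
| 0.5 | 0.5 | 0.025/0.50 = 0.050 | 1.35 | 9.2% |
| 0.5 | 0.8 | 0.025/0.215 = 0.116 | 1.81 | 14.6% |

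The ICC of change rises with ρ, so a score ICC below 0.05 gives less inflation.

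**4. Simulation under no effect, 14 practices × 8 patients per arm.**

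| ICC of change | Patient-level test of change | AIC may add practice-by-time | Practice-level test of change |
|---|---|---|---|
| 0 | 4.5% | 4.5% | 4.7% |
| 0.02 | 6.4% | 5.9% | 5.1% |
| 0.05 | 9.0% | 6.9% | 4.8% |
| 0.12 | 14.6% | 6.1% | 4.9% |

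At an ICC of change of 0.05, AIC picked the practice-by-time term in 33% of runs.

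Follow-up CRQ on arm and baseline CRQ with a practice random intercept gave 4.7% (CAC 0.8, IAC 0.5) and 5.5% (CAC 0.5, IAC 0.8), from 1,500 runs each.

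**The case against.** The strongest reply is that the section states what the random effects are for, not their exact form. It does not say that they are intercepts only, and it does not name arm-by-time as the contrast. It allows baseline CRQ as a covariate; with two visits, that points to a model of follow-up in which the practice effect does not cancel. It leaves room for AIC to bring in a practice-by-time term, and it says outright that the intracluster correlation will be accounted for. A journal article may also leave the precise structure to a fuller plan.

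Most of this stands. A reader might infer that the arms will be compared as if patients were independent and that the true error is some fixed figure well above 5%. The documents do not support that: the vulnerable model is one permitted reading, and the inflation depends on over-time correlations that appear nowhere in them.

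Three things remain. The within-patient random effect fits only the two-visit model, so that reading is the most natural one. Baseline adjustment is optional, so it cannot be relied on to rescue the test. AIC, as simulated, does not fully restore 5%. As for condensation, the article does state its random effects and its selection rule; the difficulty lies in what those words permit.

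**Conclusion.** The point holds as a conditional one. Followed on its plainest reading, the section gives a primary test in which practice-level clustering of change plays no part, contrary to its stated intent and to the design effect in the sizing. With ICC 0.05 and 8 patients per practice, the two-sided error would be 5% if practice effects are the same at both visits. It would be about 7-9% at a practice autocorrelation of 0.8 and about 9-15% at 0.5, for patient autocorrelation of 0.5-0.8. These correlations are assumed, and 0.05 is itself the upper end of the ICC range that the protocol cites. If AIC may select a practice-by-time term, the figure is about 5-7%. Under the other permitted models it is about 5%. The cancellation itself is exact and needs no assumed correlation. The sample size arithmetic is not in question.

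**What to change.** In Quantitative Analysis, replace the random-effects clause with one stated primary model for each CRQ dimension:

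- follow-up CRQ on arm and baseline CRQ, with a practice random intercept; or
- if both visits are kept as responses, practice and patient effects plus a practice-by-time random effect.

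In either case, retain the practice-level term whatever its AIC, and test the arm effect on between-practice degrees of freedom (28 − 2 = 26 after the planned losses).

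The change costs one sentence, with no new data or patients. The price is a wider interval than the intercept-only model would give. At a design effect of 1.35 it is √1.35 = 1.16, about 16% wider, and the t quantile on 26 degrees of freedom adds 2.056/1.96 = 1.05, about 5% more. The sample size already budgets for the 16%. It does not budget for the 5%, because the 32 practices reproduce with a normal approximation.

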### Primary

The primary outcome measure of the study will be health status as measured by the Chronic Respiratory Questionnaire (CRQ) [23]. This instrument was developed following interviews with people who had COPD [23]. The questionnaire has four domains: dyspnoea, fatigue, emotional function and mastery.

The validity and reliability of this tool was first investigated by Wijkstra et al. [24] who concluded that the CRQ was a valid and reliable tool. This conclusion was also confirmed by Curtis and Patrick [25] who found that the CRQ was reliable, valid and responsive to change. In addition, they claim that the CRQ is more sensitive to change than other generic health status instruments.

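### Four CRQ dimensions are each modelled as the primary response at 0.05, with no rule for turning four results into one primary conclusion; neither natural rule delivers both the 5% error and the 80% power planned

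*Protocol article*

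**What the plan says.** Three sections of the protocol article bear on this point.

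- **Outcome measures, Primary.** There is one primary outcome: "The primary outcome measure of the study will be health status as measured by the Chronic Respiratory Questionnaire (CRQ"). The section then adds: "The questionnaire has four domains: dyspnoea, fatigue, emotional function and mastery". It names no total score, lead dimension or order of testing.
- **Sample Size Estimation.** The trial is sized for a single comparison. The difference is common to the dimensions: "Previous work suggests 0.5 as the minimal clinically important mean difference for all four dimensions of the CRQ". The standard deviation is one averaged figure, "1.145 (given as arithmetic mean of 0.88, 1.06, 1.24 and 1.40 for the Dyspnoea, Fatigue, Emotion and Mastery dimensions". Alpha is 0.05, power is at least 80%, and the result is 32 practices of at least 10 patients.
- **Quantitative Analysis.** A mixed-effects model is used to "model the longitudinal change in the mean scores for each of the four dimensions of the CRQ primary response", and the section ends: "The significance level will be set at α = 0.05 for all analyses".

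No section says whether the primary conclusion needs one significant dimension, all four, or a combined score.

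**The concern.** The three sections treat the primary outcome in three ways: as one construct, as one comparison with an averaged SD, and as four separately modelled responses. The alpha sentence gives each of the four the full 0.05.

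The headline conclusion is at stake. The stated SDs give the four dimensions unequal power, so a split result, with one or two dimensions significant, is realistic. The article offers no basis for calling such a trial positive or negative, and the choice could be made with the results in hand. A rule that accepts any one dimension inflates the false-positive rate. A rule that demands all four undermines the power claim.

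**Working it through.** **Inputs from the documents.** Difference 0.5; SDs 0.88, 1.06, 1.24 and 1.40 (dyspnoea, fatigue, emotion, mastery), mean 1.145; ICC 0.05 ("the upper value of 0.05 from a range of ICC values identified within studies involving the older person in primary care"); alpha 0.05; power 80%; 32 practices of 10; losses of 20% of participants plus 4 practices; 1:1 allocation.

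**Assumed.** The correlation between the dimensions' test statistics is not in the documents. A common value r from 0 to 0.9 is shown. The ICC is taken as 0.05 for every dimension.

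**1. The plan's own figure** (normal approximation, two-sided)

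- Per arm without clustering: 2 × [1.145 × (1.960 + 0.842) / 0.5]² = 82.3.
- Analysed per practice after 20% loss: 8. Design effect: 1 + (8 − 1) × 0.05 = 1.35.
- 82.3 × 1.35 = 111.1 per arm; 111.1 / 8 = 13.9, so 14 practices per arm, 28 in total; plus 4 = 32. This matches the article.
- Power with 14 practices of 8 per arm: effective n = 112 / 1.35 = 83.0; SE = 1.145 × √(2/83.0) = 0.178; 0.5 / 0.178 = 2.81; Φ(2.81 − 1.96) = 80.3%.

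Sidedness is not stated, but a one-sided 0.05 gives 65 per arm and 26 practices, so the plan is one two-sided test at 0.05. It holds no allowance for four tests. (Rounding 82.3 up to 83 first gives 14.006 practices per arm, so the match depends on when one rounds.)

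**2. If any one significant dimension counts as success**

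Independent tests: 1 − 0.95⁴ = 18.5%. For common correlation r, with c = 1.96:

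- either direction: 1 − ∫ φ(u) [Φ((c − √r u)/√(1 − r)) − Φ((−c − √r u)/√(1 − r))]⁴ du
- benefit only: 1 − ∫ φ(u) [Φ((c − √r u)/√(1 − r))]⁴ du

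| r | Any false positive (nominal 5%) | False claim of benefit (nominal 2.5%) |
|---|---|---|
| 0 | 18.5% | 9.6% |
| 0.5 | 15.6% | 7.8% |
| 0.7 | 13.0% | 6.5% |
| 0.8 | 11.4% | 5.7% |
| 0.9 | 9.4% | 4.7% |

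**3. If all four must be significant**

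Alpha stays at or below 5%. Power per dimension, with 28 practices of 8 and each dimension's own SD:

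| Dimension | SD | Power at 0.05 | Power at 0.0125 |
|---|---|---|---|
| Dyspnoea | 0.88 | 95.5% | 87.7% |
| Fatigue | 1.06 | 85.9% | 70.6% |
| Emotion | 1.24 | 73.8% | 54.0% |
| Mastery | 1.40 | 63.3% | 42.2% |

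Joint power cannot exceed the lowest of these, 63.3%. Even with no losses (32 practices of 10), mastery reaches only 75.6%.

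**4. One test on the mean of the four scores**

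SD of the mean = ¼ √[Σs² + r((Σs)² − Σs²)], with Σs² = 5.396 and (Σs)² = 20.976.

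- r = 0.5: SD 0.908. r = 0.7: SD 1.009. r = 1: SD 1.145, the article's averaged figure.
- All four improve by 0.5 (mean shift 0.5): power 94%, 89% and 80.3% at r = 0.5, 0.7 and 1.
- Three improve (mean shift 0.375): 76% at r = 0.5, 67% at r = 0.7.
- Two improve (mean shift 0.25): 43% and 36%.

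**The case against.** The strongest reply is that the any-one-dimension rule is nowhere written. The article sets a significance level and does not say that one dimension is enough. Requiring all four is equally open, and the abstract's 0.5 units in the CRQ, with the averaged SD, even hints at one overall comparison. This stands. A reader might infer that the trial's false-positive rate simply is 13% to 19%. The documents do not support that: it needs the any-one rule and a correlation no higher than 0.7. The 19% end needs uncorrelated dimensions, which is implausible for four parts of one questionnaire, and at 0.8 to 0.9 the figure is 11% to 9%. It also counts false harm as well as false benefit.

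A second reply is that an article condenses the full protocol and that a combination rule often sits in an analysis plan. This stands only in part. A separate plan may hold such a rule, and Holm or a fixed sequence also works at an overall 0.05. But the article is not silent: it pairs "for each of the four dimensions of the CRQ primary response" with a flat 0.05 for all analyses, against one named outcome and a sample size for one test. Those statements need reconciling whatever a later plan says.

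A third reply is that the mean score redefines the endpoint after randomisation began (September 2009), and that 0.5 is given as the important difference for each dimension, not for their mean. Both facts are correct and count as costs of the fix.

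**Conclusion.** The point holds in conditional form. The article states one primary outcome and a sample size that reproduces as one two-sided test at 0.05 (80.3% power), but analyses four primary responses at 0.05 each without a decision rule.

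- Under an any-one rule, family-wise error is about 9% to 19% over r = 0.9 to 0, and 13% to 16% at 0.7 to 0.5. False claims of benefit are about 5% to 10% against 2.5%.
- Under an all-four rule, error is controlled but power is at most 63%, well short of the stated 80%.

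The first set of figures rests on an assumed common correlation; both rest on the normal approximation and the article's own SDs and ICC. Possible extra inflation from choosing covariates as needed and models by AIC is not counted. This should be fixed, but it does not show that the trial's error rate is already uncontrolled, because the rule for success is unstated rather than wrong.

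**What to change.** Before unblinding, replace the alpha sentence with wording such as:

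> The primary analysis is a single test, at two-sided 0.05, of the between-group difference in the mean of the four CRQ dimension scores at follow-up. The four dimensions are secondary outcomes, tested by the Holm procedure at a family-wise two-sided 0.05.

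This fits the averaged SD already used for the sample size and needs no extra patients. It has a price. It redefines the endpoint during the trial, so the change should be dated and justified, with a statement of why 0.5 is the relevant difference on the mean. It also dilutes an effect confined to some dimensions, as the 67% to 76% and 36% to 43% figures show.

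If the four dimensions are to stay co-primary, apply Holm across them and restate the power. The first step at 0.0125 gives 88%, 71%, 54% and 42% for dyspnoea, fatigue, emotion and mastery. At the averaged SD, power at 0.0125 is 62.4%. Restoring 80% at that level would take about 44 practices: 117 per arm × 1.35 / 8 = 19.7, so 20 per arm, 40 in total, plus 4.
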